### 2.3. Data collection, management and analysis

#### 2.3.1. Data collection methods.

We will collect data at baseline, intraoperatively and postoperatively to assess primary and secondary outcomes. Participant socio-demographic information, medical history and current medication, will be collected from their medical chart. Their education level and familiarity with VR technology will also be recorded through a preoperative questionnaire. Pre-operative anxiety levels will be assessed using the APAIS, a six-item questionnaire designed to measure both anxiety and the desire for information before surgery. The scale provides an overall anxiety score ranging from 4 to 20 and an information-seeking score ranging from 2 to 10, with higher scores indicating greater preoperative anxiety and a stronger desire for information, respectively. A postoperative questionnaire will be used to collect data on patient satisfaction. It is of note that, aside from the APAIS, both our preoperative and postoperative questionnaires are self-composed and have not yet undergone formal scientific validation.

NOL index data from the PMD-200 medical monitor will be automatically collected by the device. Other intraoperative events, such as propofol self-administration, as well as the use of fentanyl or ketamine, will be manually recorded. Postoperative outcomes will be collected through questionnaires administered to participants prior to their discharge from the PACU, at which point we will also record PACU length of stay (LOS). Adverse events of any kind will be documented when spontaneously reported or observed clinically.

We will monitor and document the number of participants who withdraw from the study. If a participant wishes to discontinue their involvement, they will be removed from the study at their request, and no further data will be collected or retained after their withdrawal.

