The attending anesthesiologist will perform PV block before surgery according to their usual practice. Only anesthesiologists with a minimum of 10 PV blocks performed within the last year will be qualified to administer this procedure to trial participants. Standardized doses of intravenous (IV) sedation (0.15 mg/kg of propofol) and IV analgesia (0.5 mcg/kg of fentanyl) will be administered to all participants prior to realization of the PV block and will be repeated if necessary. Once the block is complete, the participant is positioned supine, and the surgeon is ready for disinfection, the VR headset will be applied to those in the intervention group and their chosen scenario will begin. A dedicated research staff member will be present in the operating room throughout the procedure to manage all aspects of the VR intervention, including assisting with headset application, adjusting the VR scenarios upon patient requests, and addressing any technical issues or patient discomfort related to the VR system. Notably, the interactive VR scenarios do not require significant hand or arm movement, as they rely solely on eye-tracking software to aim within the game. The only manual action required is pressing the controller trigger at specific time points. If at any time the patient expresses a desire to discontinue VR during the surgery, we will first offer them an alternate scenario. If they reiterate their willingness to stop, with or without having experienced the new scenario, the headset will be removed for the remainder of the surgery. In case of adverse events attributable to VR gear, such as cybersickness, discontinuation of VR immersion will be at the discretion of the anesthesiologist as well as the patient.

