**Fig 1 pone.0327555.g001:**
[figure not shown]
VR headset and scenario choices. A Paperplane Therapeutics VR headset; B Scenario 1 – Calm; C Scenario 2 – Puzzle; D Scenario 3 – Action.

In both groups, the PCS protocol will consist of 0.15 mg/kg boluses of IV propofol with a lockout period of 2 minutes; additional clinician boluses may be administered based on the lead anesthesiologist’s judgment. For breakthrough pain, local anesthesia can be utilized by the surgical team. The anesthesiologist can also administer 0.5 mcg/kg doses of IV fentanyl and, if insufficient, 0.15 mg/kg doses of IV ketamine. If one of the following criteria are met, the anesthesiologist will switch the participant to general anesthesia: inadequate surgical anesthesia despite attempting all previous measures, persistent hemodynamic or respiratory instability (mean arterial pressure < 60 mmHg despite fluid resuscitation and vasopressors or SpO_2_ < 92% that does not respond to non-invasive oxygenation methods) and any surgical complication requiring general anesthesia.

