#### 2.1.4. Outcomes.

The primary outcome is the time-adjusted and weight-adjusted average or median self-administered dose of propofol in mcg/kg/min.

Secondary outcomes include

Initial enthusiasm at the idea of using a VR headset during surgery assessed by research staff on a 10-point Likert scale for all participants, prior to intervention allocation as part of a questionnaire;Level of anxiety and information requirement measured preoperatively by research staff using the Amsterdam Preoperative Anxiety and Information Scale (APAIS) [18];Incidence of intraoperative and postoperative adverse events such as bradycardia (heart rate < 50 bpm), desaturation (SpO_2_ < 92%) and hypotension (MAP < 60) as well as subjective adverse events, such as cybersickness or nausea documented intraoperatively by the anesthesiologist and research staff based on real-time clinical observation or patient self-reporting;Average or median total time, in minutes, during which the VR headset was worn, as well as the percentage of that time relative to the overall duration of the surgery, recorded by dedicated research staff in the operating room using a time log;Average or median total duration in minutes spent by the patient on the VR scenario chosen, and the order in which VR scenarios were presented, recorded by dedicated research staff in the operating room using a time log and a case report form (CRF);Percentage of patients that switched scenarios;Percentage of patients that removed the headset before the end of the surgery;Percentage of patients requiring additional local anesthesia;Weight-adjusted average or median administration of intraoperative IV fentanyl in mcg/kg;Weight-adjusted average or median administration of intraoperative IV ketamine in mg/kg;PACU length of stay (LOS) measured from PACU admission to PACU discharge, based on the PACU nursing records;Ease of use of the technology and enjoyment of the first scenario chosen assessed post-operatively on a 10-point Likert scale in the intervention group only as part of a postoperative questionnaire administered by dedicated research staff;Overall satisfaction with the experience assessed post-operatively on a 10-point Likert scale in both groups as part of a postoperative questionnaire administered by dedicated research staff.Exploratory outcomesNOL index readings over time per patient, recorded continuously intraoperatively via a finger probe, automatically stored and extractable by dedicated research staff from the PMD-200 monitor with precise timepoints. NOL index spikes will be defined;PCS bolus administration timepoints, automatically recorded by the pump device and extracted by dedicated research staff.

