### 2.2. Assignment of interventions

Electronic randomization of the participants will be performed by an independent third party, using the National Cancer Institute’s Clinical Trial Randomization tool [24]. Specifically, we will randomize participants in a 1:1 ratio using a maximal randomization method, allowing a maximum tolerated imbalance of 3. The randomization sequence will then be implemented in the REDCap application (Vanderbilt University) [25]. Each participant’s allocation will be sealed in an opaque envelope and handed to the dedicated research staff not involved in patient care. The envelope will be opened at the patient’s entry into the operating ward, after confirming that the surgery will be performed under regional anesthesia. The intervention will not be blinded to participants or personnel after allocation.

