#### 2.3.2. Data management.

Data from this study will be collected and managed using REDCap electronic data capture tools hosted at Maisonneuve-Rosemont hospital. Research staff will systematically double-check all data entries for completeness and accuracy before final submission. Each participant will be assigned a unique identification number upon enrollment to maintain confidentiality and ensure anonymization.

All collected data will be securely stored on a designated research computer, which will remain offline and be located in a restricted area in Maisonneuve-Rosemont hospital. Notably, this computer will utilize the integrated event-tagging system of the PMD-200 or the BetterCare software (provided by Dräger, Lübeck, Germany), which is connected to the Dräger anesthesia workstation. Usage of this computer will be limited to authorized research personnel, who will need encrypted logins to access study data.

To promote data quality, double data entry will be implemented for our primary outcome. Furthermore, regular, informal audits will be conducted by the research team to verify the accuracy of the study data.

After study completion, electronic data will be retained on secure, encrypted servers for a period of 7 years, as per local institutional and ethical guidelines. Physical copies of patient information, such as consent forms, will be securely stored in a locked file cabinet in the anesthesiology department.

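### The primary outcome, self-administered propofol, is to be recorded by hand in an unblinded trial although the pump's automatic bolus record is already to be extracted for an exploratory analysis

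*Protocol article*

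**What the plan says.** - **Primary outcome (section 2.1.4):** "The primary outcome is the time-adjusted and weight-adjusted average or median self-administered dose of propofol in mcg/kg/min".
- **Capture, data collection section (2.3.1):** NOL data are collected by the device. The next sentence reads: "Other intraoperative events, such as propofol self-administration, as well as the use of fentanyl or ketamine, will be manually recorded".
- **Capture, exploratory outcomes (section 2.1.4):** "PCS bolus administration timepoints, automatically recorded by the pump device and extracted by dedicated research staff".
- **PCS setting (section 2.1.3, text after Fig 1):** "the PCS protocol will consist of 0.15 mg/kg boluses of IV propofol with a lockout period of 2 minutes". Clinician boluses are allowed in addition.
- **Blinding (section 2.2):** "The intervention will not be blinded to participants or personnel after allocation".
- **Staff in the room (section 2.1.3):** "A dedicated research staff member will be present in the operating room throughout the procedure to manage all aspects of the VR intervention".
- **Data checks (section 2.3.2):** "To promote data quality, double data entry will be implemented for our primary outcome", and "Research staff will systematically double-check all data entries for completeness and accuracy before final submission". Informal audits by the research team are also planned.

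No section names the pump record as the source of the primary outcome, and none plans a comparison of the manual record with it.

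**The concern.** The same boluses are given two capture methods. The data collection section assigns the primary outcome to manual recording. The automatic record appears only under the exploratory outcomes.

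This matters because nobody in the operating room is blinded. Section 4.1.1 defends the open-label design on the ground that PCS limits the anesthesiologist's influence on how much propofol is given. That argument concerns administration and does not reach recording. A machine record of the boluses would extend the protection to the measurement itself.

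The listed checks work on what has been entered. Double entry finds transcription errors. It would not reliably recover a bolus that was never written down, and it would not reliably show that a clinician bolus had been written down as a patient bolus. If such errors were more frequent in one arm, the treatment comparison would be biased. If they were random and equally frequent in both arms, the cost would be some power.

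**Working it through.** **1. The plan's own figure.** The plan gives no figure for recording error. Its only related figure is the sample size in section 2.1.6: 90 participants for a 30% reduction, two-sided 0.05, 80% power, raised to 100. No SD is stated, so 90 can only be back-solved. With 45 per arm the two-sample t-test needs d = 0.597. A 30% reduction then implies SD / control mean = 0.30 / 0.597 = 0.50. With that assumed coefficient of variation the t-test returns 90, and 90 / (1 − 0.10) = 100. The point here does not depend on this figure, which is used only in step 4.

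**2. Can the pump record supply the primary outcome?** Each PCS bolus is a fixed 0.15 mg/kg = 150 mcg/kg (section 2.1.3). Hence

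self-administered dose (mcg/kg/min) = delivered PCS boluses × 150 / duration (min).

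A count of delivered boluses is enough for the numerator. The 2-minute lockout caps the rate at 150 / 2 = 75 mcg/kg/min.

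**3. What one missed bolus does.** Duration is an assumption, as the document gives none.

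| Assumed duration | Shift in that patient's value |
|---|---|
| 60 min | 150 / 60 = 2.50 mcg/kg/min |
| 90 min | 150 / 90 = 1.67 mcg/kg/min |
| 120 min | 150 / 120 = 1.25 mcg/kg/min |

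Suppose one bolus is missed in every patient of one arm and none in the other, at 90 minutes. Control means are assumed:

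| Assumed control mean (mcg/kg/min) | 30% effect | 1.67 as share of the effect |
|---|---|---|
| 75 (lockout ceiling) | 22.5 | 7% |
| 30 | 9.0 | 19% |
| 20 | 6.0 | 28% |

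The scenario is severe at the low end. A control mean of 20 over 90 minutes is 20 × 90 / 150 = 12 boluses, so one miss is 1 / 12 = 8% of a control patient's dose. With a 30% reduction a VR patient takes 8.4 boluses, and one miss is 1 / 8.4 = 12%.

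**4. Illustration on the test** (assumptions: coefficient of variation 0.50, 45 per arm, common SD).

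| Share of dose missed, one arm only | Missed in VR arm, no true effect: type I error | Missed in control arm, true 30% reduction: power |
|---|---|---|
| 0% | 5.0% | 80.0% |
| 2% | 5.4% | 74.4% |
| 5% | 7.5% | 64.6% |
| 10% | 15.4% | 46.3% |

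Random error that is equal in both arms costs much less. With error SD at 10%, 20%, 30% or 50% of the true SD, power is 79.6%, 78.4%, 76.5% or 70.7%. The exposure that matters is therefore error that differs between arms.

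**The case against.** The strongest reply is that the two sections are compatible. Manual recording may mean that staff enter or tag events on the research computer, including values read from the pump, and the protocol does say that research staff extract the pump record. It also does not restrict that record to exploratory use. This reading is possible, but the document does not state it. Section 2.3.1 sets manual recording against automatic device capture, and the sentence that settles the matter is the same on either reading.

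A second reply is that the data checks are broader than double entry: entries are reviewed for completeness and audited. That is true, but none of these checks is stated to use the pump as the reference.

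A third is that a condensed article leaves source-data detail to the full protocol or case report form. That covers matters such as clock synchronisation. It does not cover a capture method that the article itself states for its primary outcome.

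Three stronger readings go beyond the text:

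- **That missed boluses would favour VR.** A reader might infer this because the staff member in the room also runs the headset. Section 2.3.1 does not say who records boluses, and section 2.1.3 does not say that this person counts them. A difference between arms is possible; its direction is not shown.
- **That manual times would spoil the NOL analysis.** Section 2.1.4 assigns automatically recorded bolus times to that analysis, and the NOL monitor stores its own readings with times.
- **That the pump holds a complete dose record.** The text speaks of bolus timepoints. It does not say whether delivered boluses are separated from locked-out presses, so this must be confirmed before the log is adopted.

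**Conclusion.** The point holds as an avoidable weakness in how the primary outcome is captured, together with an inconsistency between sections 2.1.4 and 2.3.1. It is not evidence that the result will be biased.

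The document fixes three things: the manual recording, the automatic record of bolus times, and the absence of blinded personnel. The sizes do not come from it. The range of 7% to 28% rests on a 90-minute case, control means from 75 down to 20 mcg/kg/min, and one missed bolus in every patient of one arm only. The type I error and power figures also rest on a coefficient of variation back-solved from the sample size. They show that a modest imbalance in omissions would matter, not that one is expected.

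The change deserves to be made because it replaces the stated method with a more objective one whose extraction is already planned.

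**What to change.** Reconcile sections 2.1.4 and 2.3.1 with a statement to this effect:

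1. The source of the primary outcome is the pump's log of delivered PCS boluses, exported for each patient. The dose is delivered boluses × 0.15 mg/kg, divided by duration.
2. Before adoption, the team confirms on the pump in use that the log separates delivered boluses from locked-out presses.
3. The manual record is kept as a cross-check and as backup if the log fails. Discrepancies are resolved by a stated rule, and the report says in how many patients of each arm the manual record was used.

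Clinician propofol boluses, fentanyl and ketamine can still be recorded by hand, as they are not part of the self-administered dose.

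The cost is small: a short edit to the protocol, a check of the pump's log and an export already foreseen for the exploratory outcome. The sample size stays at 90, raised to 100, and no treatment or assessment changes.

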#### 2.4.2. Potential harms.

The devices used in the study include a VR headset wirelessly paired with a tablet for broadcasting immersive scenarios. These devices do not interfere with intraoperative monitoring, and the risk of adverse events associated with their use is very low.

Any incidence of adverse effects, spontaneously reported or directly observed, will be documented and assessed as part of our secondary outcomes.

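### Nausea and other subjective adverse events are collected only passively in an unblinded trial, and a staff duty to address discomfort is described only for VR, so their detection may differ between arms

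*Protocol article*

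**What the plan says.** The protocol article describes how adverse events are collected in three places, and they agree.

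- Section 2.3.1 (Data collection methods): "Adverse events of any kind will be documented when spontaneously reported or observed clinically".
- Section 2.4.2 (Potential harms): "Any incidence of adverse effects, spontaneously reported or directly observed, will be documented and assessed as part of our secondary outcomes".
- Section 2.1.4 (Outcomes): cybersickness, nausea and similar events are "documented intraoperatively by the anesthesiologist and research staff based on real-time clinical observation or patient self-reporting".

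None of these describes a standard question, a symptom scale or a timed prompt. Section 2.3.1 gives patient satisfaction as the purpose of the postoperative questionnaire, and section 2.1.4 adds ease of use and enjoyment of the first scenario for the VR arm.

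On staffing, section 2.1.3 (Interventions) states: "A dedicated research staff member will be present in the operating room throughout the procedure to manage all aspects of the VR intervention". The listed duties include "addressing any technical issues or patient discomfort related to the VR system". No matching duty is described for control participants.

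On blinding, section 2.2 states: "The intervention will not be blinded to participants or personnel after allocation".

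**The concern.** The incidence of adverse effects, with cybersickness and nausea named, is a secondary objective in section 1.2. The introduction presents VR as a possible low-risk adjunct or alternative to sedation. Section 2.3.3 summarises categorical variables by group and provides confidence intervals for proportions, so readers will compare nausea between arms.

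When a symptom is counted only if the patient mentions it or someone notices it, the recorded rate is the true rate multiplied by the chance of detection. Three features of the plan could make that chance unequal:

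- VR participants have someone whose task includes VR-related discomfort. They also have natural occasions to speak up, such as a scenario change or headset removal.
- Everyone who reports or records events knows the allocation. Section 4.1.1 argues that patient-controlled sedation limits bias in propofol dosing. It offers no comparable safeguard for symptom recording.
- If the primary hypothesis is right, controls take more propofol and may be less likely to volunteer symptoms. This is inference; the article does not say it.

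There is also a labelling problem. The Discussion describes cybersickness as a type of nausea, while sections 1.2 and 2.1.4 list the two separately. The same symptom could be recorded as cybersickness under VR and as nausea in a control.

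**Working it through.** **1. Which outcomes are exposed.** Section 2.1.4 defines the objective events by numeric limits: "bradycardia (heart rate < 50 bpm), desaturation (SpO_2_ < 92%) and hypotension (MAP < 60". Section 2.1.3 applies the same standard monitoring to all participants, so these events do not depend on who volunteers a complaint. The primary outcome is a self-administered propofol dose and is not collected this way. Cybersickness has no control counterpart. The main between-arm comparison exposed is therefore nausea. The staff duty belongs to the operating room, so it gives no reason to expect unequal detection in the PACU. That leaves mainly intraoperative nausea.

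**2. What the text establishes about the arms.**

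| Question | VR arm | Control arm |
|---|---|---|
| Collection rule (2.1.4, 2.3.1, 2.4.2) | passive | passive |
| Named recorders (2.1.4) | anesthesiologist and research staff | same; no arm restriction |
| Staff duty towards discomfort (2.1.3) | yes, if VR-related | none described |
| Research staff in the room throughout | stated | neither stated nor excluded |
| Patients questioned about symptoms | not stated | not stated |

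The asymmetry rests on the third row and the lack of blinding. The fourth row is an open question.

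**3. How large the effect could be.** The article gives no nausea rate and no detection probability, so there is no plan figure to reproduce. All rates below are assumptions. The number per arm is 100/2 = 50, from the 1:1 allocation.

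Formula: recorded rate = true rate × detection probability. With equal true rates, the spurious risk ratio is simply the ratio of the two detection probabilities.

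True nausea 20% in both arms, detection under VR 0.9:

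| Detection, controls | Recorded, controls | Recorded, VR | Difference | Risk ratio |
|---|---|---|---|---|
| 0.7 | 0.20 × 0.7 = 14% | 0.20 × 0.9 = 18% | 4 points | 0.9/0.7 = 1.29 |
| 0.6 | 0.20 × 0.6 = 12% | 18% | 6 points | 0.9/0.6 = 1.50 |
| 0.5 | 0.20 × 0.5 = 10% | 18% | 8 points | 0.9/0.5 = 1.80 |

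Changing the true rate, with detection held at 0.9 against 0.6, gives 9% v 6% at a true rate of 10% and 27% v 18% at 30%. The spurious difference is then 3 and 9 points. If detection is equal, for example 0.8 in both arms, the risk ratio is 1.00 at any true rate.

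**4. Against sampling noise.** With 50 per arm and a normal approximation, the chance that a true rate of 20% in both arms produces a nominally significant VR excess (two-sided 0.05) is about 8% for detection 0.9 v 0.7 and about 21% for 0.9 v 0.5. Without bias, the nominal chance in that direction is 2.5%. For 27% v 18%, the standard error of the difference is √[(0.27 × 0.73 + 0.18 × 0.82)/50] = √(0.3447/50) = 0.083. A 9-point artefact is therefore about one standard error. The distortion is more likely to shift the estimate and its interval than to produce a significant result.

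**The case against.** A reader might infer that detection does differ between the arms, or that VR participants are prompted for symptoms and controls are not. The text supports neither. Section 2.1.3 has staff respond to discomfort and to patient requests; it does not say they ask about nausea. Section 2.1.4 names the recorders of subjective events without limiting them to one arm. Other passages suggest that research recording takes place in control cases too: section 2.1.3 sends all intraoperative data and events to the research computer, section 2.2 gives every allocation envelope to research staff, and section 2.3.1 has propofol self-administration, fentanyl and ketamine recorded by hand. This objection stands, and the point goes no further than that detection may differ.

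A second objection is that the likely bias makes VR look worse, so it works against a low-risk claim and cannot falsely support one. For closer attention or lighter sedation under VR, that is right. Labelling works the other way: if nausea under VR is filed as cybersickness, the VR nausea count falls.

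Third, the questionnaire and case report form are not shown, and an article may leave out their items. That is fair as to item content. The passive rule itself, however, is stated outright and consistently in three sections.

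Fourth, asking in the PACU about symptoms during surgery brings in recall, which may depend on how sedated the patient was and so could also differ by arm. This stands and shapes the fix.

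**Conclusion.** The point holds as a limited one. The plan fixes passive collection of subjective adverse events for a stated secondary outcome in an unblinded trial, and describes a duty towards discomfort only for the VR intervention. Detection of nausea, chiefly during surgery, may therefore differ between arms, and the most plausible direction is an inflated VR rate. The size is unknown. Under the assumed detection gaps the spurious risk ratio runs from 1.29 to 1.80, and it is 1.00 if detection turns out equal. A reader should not conclude that the safety comparison as a whole is unsound: bradycardia, desaturation and hypotension rest on numeric limits under common monitoring, and the primary outcome and sample size are untouched. This is an inexpensive improvement and not a condition for the trial to proceed.

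**What to change.** Section 2.3.1 already states: "Postoperative outcomes will be collected through questionnaires administered to participants prior to their discharge from the PACU". Section 2.1.4 confirms that both groups complete the postoperative questionnaire. Using that form:

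1. Add identical yes/no items for both arms, for example nausea, dizziness, and headache or visual discomfort, each asked for the surgery and for the PACU stay.
2. Count nausea the same way in both arms, whether or not it is also labelled cybersickness. Report cybersickness separately as a VR-arm description.
3. State the research staff's presence and recording role in control cases, and apply the same intraoperative recording there as in VR cases.
4. Report the solicited between-arm comparison alongside the real-time record, without replacing it. Agreement between the two would support the comparison; disagreement would show that the method of collection matters.

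Cost: three symptoms at two periods make six ticks on a self-composed form, plus research staff time in control cases if they are not already there. Reported rates will rise slightly in both arms because symptoms are asked about. Recall of intraoperative symptoms may depend on depth of sedation, which is why both sources should be shown. Treatment and the primary analysis do not change.
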